#### Safety: complication rate during hospitalization

A complication rate during hospitalization will be calculated to determine the safety of C1-INH. This rate includes serious adverse events possibly related to study medication. This includes venous thromboembolic events (deep venous thrombosis and pulmonary embolism), myocardial infarction, ischemic stroke, meningitis, pneumonia, and sepsis. Patients will be assessed daily by a blinded physician/nurse for these complications. Vital signs will be monitored closely and potential adverse reactions to the experimental treatment will be picked up immediately at the ICU.

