**Fig. 1 Fig1:**
[figure not shown]
Contact, complement, coagulation, and fibrinolytic systems and targets of C1-INH. *Abbreviations*: MAC, membrane attack complex; HMWK, high-molecular-weight kininogen; C1-INH, C1-inhibitor; t-PA, tissue plasminogen activator; MASPs, mannose-associated serine protease. *Explanation*: C1-INH is directed at all three pathways of the complement system, but has also an effect on the contact, fibrinolytic, and coagulation system

High-quality preclinical evidence suggests a significant role of the complement system in the pathophysiology of neuroinflammation. As complement inhibition is potentially an important aspect of TBI treatment to attenuate neuroinflammation, the CIAO@TBI multicenter, randomized, blinded, placebo-controlled trial aims to assess the safety and efficacy of C1-INH in TBI patients. It is hypothesized that C1-INH can be beneficial in the treatment of s-TBI by decreasing the detrimental neuroinflammation and preventing secondary brain injury to ensure a more favorable functional outcome and a less hampered quality of life for the future TBI patients.

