### Trial population and eligibility

All TBI patients presenting to participating hospitals are potentially eligible for this trial. The inclusion criteria are (1) age > 18 years, (2) clinical diagnosis of TBI with GCS < 13 on admission (with visible intracranial pathology on CT), and (3) invasive intracranial pressure monitoring by intra-parenchymatous transducer or ventricular catheter placement and management of increased ICP for at least 24 h. The exclusion criteria are (1) a clear, non-traumatic cause of low GCS on admission (e.g., toxic or cardiac cause); (2) not expected to survive more than 24 h after admission with the decision to abstain from aggressive treatment and induce palliative care; (3) brain death on arrival in the participating centers; (4) severe pre-trauma disability, defined as being dependent on other people; (5) known prior history of sensitivity to blood products or C1-INH; (6) patients with a history of hereditary angioedema (if known at admission); (7) patients with a history of thrombosis (deep vein thrombosis, cerebral venous sinus thrombosis, or pulmonary embolism) (if known at admission); and (8) patients that are pregnant (if known at admission).

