#### Safety and adverse event analysis

Safety analyses, as part of the primary endpoint, will be based on the safety set, consisting of the pre-defined SAEs, and will comprise standard descriptive methods. Changes from baseline will be summarized using standard statistical characteristics and shift tables. Details of the pre-defined SAEs, signs, and symptoms will be collected including details of onset, resolution, frequency, severity (mild, moderate or severe), seriousness, relationship to the drug, effect on the study drug, treatment administered, and outcome. Moreover, suspected unexpected serious adverse reactions (SUSARs) will be registered.

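### The events listed for the primary safety rate omit cerebral venous sinus thrombosis, hypersensitivity and bleeding, and the protocol article does not settle whether the list is closed

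*Protocol article*

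**What the plan says.** The section Safety: complication rate during hospitalization defines the safety part of the primary endpoint in two consecutive sentences. The first is general: "This rate includes serious adverse events possibly related to study medication". The second names events: "This includes venous thromboembolic events (deep venous thrombosis and pulmonary embolism), myocardial infarction, ischemic stroke, meningitis, pneumonia, and sepsis". A blinded physician or nurse checks each patient daily for the complications so named. The section closes by saying that possible reactions to the study treatment will be noticed at once in the ICU, but it does not say that they enter the rate.

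Safety and adverse event analysis fixes what is analysed: "Safety analyses, as part of the primary endpoint, will be based on the safety set, consisting of the pre-defined SAEs". The methods are descriptive, and SUSARs are registered in addition.

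Three other places bear on which harms matter:

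- Trial population and eligibility excludes "patients with a history of thrombosis (deep vein thrombosis, cerebral venous sinus thrombosis, or pulmonary embolism) (if known at admission" and, separately, those with "known prior history of sensitivity to blood products or C1-INH". It also requires an intracranial abnormality on CT.
- The Fig. 1 legend says that C1-INH acts on complement "but has also an effect on the contact, fibrinolytic, and coagulation system".
- Secondary endpoints includes between-group comparisons of PT, aPTT, platelets, d-dimer and fibrinogen, and a DIC score. It contains no clinical bleeding event.

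**The concern.** The listed events are thrombotic, ischaemic or infectious. None is haemorrhagic and none is allergic, and the venous group is narrower than the one in the exclusion criteria.

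Safety is half of the trial's main objective, the section on data and safety monitoring describes this phase II trial as focused on safety, and the results are meant to inform a phase III trial. If C1-INH increased cerebral venous sinus thrombosis, serious hypersensitivity or intracranial bleeding, the headline safety comparison might not show it. The trial would follow coagulation in the laboratory without a pre-specified comparison of clinical bleeding.

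**Working it through.** **No plan figure depends on the list.** The article states no sample size, event rate or threshold for safety. Its N of 106 comes from TIL (difference 2.2, SD 3.2, two-sided 0.05, 90% power, about 10% loss). A two-sample t-test needs 45.4, so 46 per arm; 46 / 0.9 = 51.1, so 52 per arm and 104 in total, within 2 patients of 106. Changing the safety list does not alter this.

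**Events set against the text.**

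| Event | Where the article points to it | Named in the primary safety list? |
|---|---|---|
| Deep vein thrombosis | Exclusion 7 | Yes |
| Pulmonary embolism | Exclusion 7 | Yes |
| Cerebral venous sinus thrombosis | Exclusion 7 | No |
| Hypersensitivity | Exclusion 5; the product is purified from human plasma | No |
| Clinical bleeding | Indirectly: stated effects on coagulation and fibrinolysis, coagulation tests, CT lesion required | No, and not a secondary endpoint |

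**Open or closed list?**

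1. *Closed reading.* The daily check is for the named complications, and the analysis section uses pre-defined SAEs. An unnamed event then cannot enter the rate.
2. *Open reading.* The general sentence governs and the named events are examples. A serious unnamed event enters if someone judges it possibly related to the study drug. The daily check is still not directed at it. Growth of a haemorrhage in an injured brain is readily put down to the injury, so entry would depend on a causality judgement that could easily go the other way.

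On the first reading the omitted events are outside the rate; on the second their inclusion is uncertain. The rate need not reflect them on either.

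**What a by-arm table of 53 per group could show.** The true rates below are assumptions; the article gives none.

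- With no events among 53 treated patients, the one-sided 95% upper bound is 1 − 0.05^(1/53) = 5.5%.
- The chance of at least one event is 1 − (1 − p)^53: 41% at p = 1%, 66% at 2%, 93% at 5% and 99.6% at 10%.
- Power of a two-sided 5% test, by the normal approximation with pooled null variance, is 16% for 5% v 10% and 30% for 10% v 20%.

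So if these events occur in even a few percent of patients, some will probably be seen, but a formal test would have little power. That argues for a pre-specified descriptive table by arm, not for another test.

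**The case against.** The strongest reply is that the general sentence about possibly related SAEs stands before the list and may keep it open, so that a serious anaphylaxis, sinus thrombosis or bleed judged possibly related would count. This stands as far as it goes: the article does not call the list exhaustive. But it then disagrees with the analysis section, and that disagreement itself needs resolving.

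A reader might infer that the safety objective can be met while these harms go uncounted. The documents do not support that. No pass criterion for safety is stated. (S)AEs are monitored in hospital and SUSARs are registered. The DSMB sees unblinded (S)AEs, SUSARs and mortality, meets after 10, 30, 60 and 106 inclusions, and can advise stopping. Serious bleeding could also show indirectly in mortality, midline shift, ICP burden, TIL or GOSE. None of these, however, is a pre-specified comparison of the events themselves between arms.

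A reader might also take bleeding as a harm the protocol names. It does not; the text describes effects on coagulation and fibrinolysis without giving a direction of clinical effect, and the tests are exploratory. Bleeding is an inference from mechanism and population. Likewise, an exclusion criterion need not be mirrored among the outcomes, so the mismatch over sinus thrombosis and hypersensitivity is a discrepancy to resolve and not proof of error.

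Finally, this is a condensed article, and fuller event definitions may sit in protocol version 7.0, which is not shown. That limits confidence about what will be collected. It does not excuse the discrepancy, because the article itself sets out the components of a primary endpoint.

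**Conclusion.** The point holds in limited form and is worth acting on. The definition of the primary safety rate and the safety analysis section do not agree on whether the event list is closed. On either reading the rate need not reflect cerebral venous sinus thrombosis, serious hypersensitivity or bleeding. The first two are tied to the article's own exclusions; the third is a reasonable concern, not a contradiction.

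The gap concerns the pre-specified comparison by arm. It does not mean that such events would go unrecorded. Its size in patients cannot be derived, because no event rates are given, and the rates used in the calculations above are illustrations and not evidence of harm. The TIL analysis, the GOSE analysis and the sample size are untouched.

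**What to change.** Reconcile Trial population and eligibility, Safety: complication rate during hospitalization, and Safety and adverse event analysis as follows.

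1. State whether the list of pre-defined SAEs is closed. If it is open, say who decides that an unnamed event counts and on what basis.
2. Add cerebral venous sinus thrombosis and serious hypersensitivity or infusion reactions to the pre-defined SAEs.
3. Report new or progressive intracranial haemorrhage, on CT done as part of care, and other major bleeding by arm as a separate pre-specified safety outcome. Keep it outside the composite, so that bleeding due to the injury itself cannot swamp the other components.
4. Show every component by arm beside the total.

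The cost is a few CRF fields, a working definition of progression with a reading standard for clinically indicated CT (reading midline shift does not supply one), and a slightly higher reported complication rate. No extra patients or scheduled scans are needed, and daily assessment is already planned.

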### Secondary endpoints

Secondary endpoints include all-cause mortality rate during the study period (proportion), ICP burden (pressure and time dose (PTD) calculated as the area under the curve above ICP threshold of 20 mmHg) during ICP monitoring, occurrence of CT midline shift during hospitalization (proportion), ICU and hospital length of stay (median), and hospital discharge location (proportion). Additionally, the GOSE will be assessed at discharge and 3 and 12 months follow-up. Quality of life will be assessed using the Quality of Life after Brain Injury Scale (QoLiBri) [45, 46]. The QoLiBri is the first TBI disease-specific quality of life outcome tool that is cross-culturally developed and validated in large populations. This questionnaire consists of 37 items designed to assess the health-related quality of life (HRQol) after TBI, and the median score will be compared at 3, 6, and 12 months after trauma. To assess health and well-being, the Short Form (SF)-36 [47] and 5-Level EuroQol 5-Dimensional Questionnaire (EQ-5D-5L) will be assessed [48]. SF-36 is a subjective measure of health and well-being, and the median score will be compared at 6 and 12 months after head trauma. The EQ-5D-5L is a 5-dimensional generic instrument assessing health-related quality of life and health status and generates an index of health. This questionnaire will be filled out by patients at 6 and 12 months follow-up, and the median score will be compared between the groups. The cost-effectiveness of the C1-INH will be analyzed with the median costs per quality-of-life year (QALY), based on the iMTA Productivity Cost Questionnaire (iPCQ) and iMTA Medical Consumption Questionnaire (iMCQ) at 3, 6, and 12 month follow-up [49]. Blood and CSF samples will be used (up to 96 h after C1-INH administration) to measure complement activation in an exploratory fashion, using WIESLAB, C4b/C, C3b/C, and C5b-9 ELISA assays. Neurological damage will be analyzed with glial fibrillary acidic protein (GFAP) and ubiquitin C-terminal hydrolase-L1 (UCHL-1) biomarkers. To explore the interactions of the complement system with the coagulation cascade, routinely, PT, aPPT, PLT, d-dimer, and fibrinogen tests will be performed and compared between the treatment groups. The Disseminated Intravascular Coagulation (DIC) Score will be calculated for all patients as proposed by the Scientific and Standardisation Committee of the International Society on Thrombosis and Haemostasis [50]. Lastly, general inflammatory markers, TNF-alpha, and interleukins will be analyzed to explore the effect of C1-INH on neuroinflammation.

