## Background

Traumatic brain injury (TBI) is a major cause of death and disability around the world. In Europe, over one million traumatic brain injury (TBI) patients are admitted to the hospital yearly, of whom 75,000 people die [1, 2]. This debilitating morbidity leads to enormous societal costs [3]. Therapies and guidelines that have been demonstrated to improve the outcomes after TBI are still limited, especially in the management of severe TBI (s-TBI), defined by Glasgow Coma Scale (GCS) 3–8 [4]. Patients with s-TBI have a high mortality rate, estimated at 30–40% in observational studies [1]. Survivors of s-TBI experience a substantial burden of physical, psychiatric, emotional, and cognitive disabilities that disrupt their lives, their proxy family members, and their social surroundings. Adequate treatment strategies are therefore pivotal. TBI comprises a dynamic pathophysiology that evolves over time, consisting of primary injury after the traumatic hit, followed by systemic disorders which lead to secondary injury [5]. The overshooting inflammatory response and delayed formation of brain edema, mostly seen around the third day after trauma, are characteristics of secondary brain injury, which are in turn related to a complicated clinical course, delayed recovery, late morbidity, and mortality in TBI [6–8].

The complement system forms the first line of defense against microorganisms and is critical in sensing tissue damage. Complement activation can be mediated by three distinct pathways: the classical pathway, the lectin pathway, and the alternative pathway [9]. Multiple experimental studies have identified a pathophysiologic role of the complement system in contributing to posttraumatic neuro-inflammation, disruption of the blood-brain barrier, secondary neuronal damage, and neuronal cell death after TBI [10–14]. Activation of the complement system in s-TBI results in a cascade of events including increased vascular permeability and activation of microglia and astrocytes, ultimately resulting in inflammatory reactions in and around contusion areas [15, 16]. In addition, it triggers a sustained degenerative mechanism of reduced dendritic and synaptic density and inhibited neuroblast migration several weeks after TBI in animal models [17]. In severe TBI patients, elevated complement factors have been found in the serum [18, 19] and in the ventricular cerebrospinal fluid (CSF) directly after initial trauma [20, 21].

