### Primary endpoints

#### Efficacy: Therapy Intensity Level (TIL) Scale

To measure the direct effect on the mechanism of action of C1-INH, our primary endpoint focuses on a decrease in ICP. ICP has been used as a surrogate endpoint for inflammation and testing of neuroprotective agents in many prematurely halted or failed clinical trials [37]. This might be due to the fact that ICP is an early surrogate marker during TBI but confounded by the modern neuro-ICU practices through escalating interventions (such as decompressive craniectomies (DC)) to immediately mitigate surges in ICP resulting in reduction of its sensitivity, as representing “severity of disease.” Therefore, this trial will focus on the intensity of ICP-targeted therapy based on the Therapy Intensity Level (TIL) Scale [38, 39]. The TIL Scale is designed to integrate all known and relevant ICP directed treatments into a single-summary score and was developed as part of the Interagency Common Data Elements scheme [38]. Since its introduction, the novel TIL Scale has been widely used in neurotrauma research, with excellent inter- and intra-rater reliability with minimal measurement errors [39]. The TIL Scale includes eight ICP treatment modalities each with a certain numerical score. Added together, TIL ranges between 0 and 38 points with a right-skewed distribution. Specifically, TBI patients admitted to the ICU have an average TIL score of 8.2 (SD 3.2), while general trauma patients on the ICU have a score of 2.2 (SD 0.9) [39]. The daily score will be calculated based on the highest score in each item per day (TIL24), to provide a metric on the maximal therapeutic intensity for ICP management for that day. The TIL score will be based on the highest TIL24 during the days an ICP monitor is in place (TILmax) and will be scored by a trained research team, and according to an SOP, thereby optimizing inter- and interrater reliability.

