### Statistical analysis

The trial profile will be summarized using a Consolidated Standards of Reporting Trials (CONSORT) flow diagram, including the reasons for non-eligibility and non-enrollment [52]. The data will be analyzed on an intention-to-treat basis with all randomized patients included in the analysis. Baseline variables will be summarized using descriptive statistics. In line with the IMPACT recommendations, the investigators plan to analyze the primary outcome TIL by using a linear model with covariate adjustment for age, GCS, and pupillary reactivity to adjust for baseline imbalances and to optimize statistical efficiency [53]. TIL will be analyzed as the TILmax for each patient, and the median for each group will be calculated. The treatment effect estimated will be based on the adjusted mean differences including 95% confidence intervals. To maintain the 5% familywise error rate, while still comparing the multiple clinically relevant endpoints, we will use a serial gatekeeping approach for statistical testing [54]. Analysis of GOSE at 6 months, as an ordinal outcome, will be done only if a significant difference in TIL is found. The co-primary endpoint GOSE will not primarily be used to declare the study success. For the analysis of GOSE at 6 months, covariate adjustment for the strongest predictors of outcome in TBI will be performed as mentioned above. The effect estimate will be an adjusted proportional odds ratio with 95% confidence interval for the shift in the direction of a better outcome on the GOSE. The ordinal regression model assumes that the odds ratio for each potential cut of the GOSE is constant no matter which cutoff point is taken (proportional odds assumption). Although the common odds ratio is formally only valid if the proportional odds assumption is met, the common odds ratio can be interpreted as a summary measure of treatment effect, even if the odds ratios differ by cutoff [55, 56]. In this study, the resulting single, common odds ratio can be interpreted as the average shift over the GOSE scale at 6 months caused by C1-INH compared to placebo [56].

Secondary analyses will be compared between the treatment groups using unadjusted and adjusted (ordinal) logistic and linear regression. Time-to-event analyses will be undertaken using Kaplan-Meier curves, as well as Cox proportional hazards regression models.

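### Length of stay counts an in-hospital death as a short stay, and death before the peak could lower TILmax; both endpoints need an analysis that accounts for death

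*Protocol article*

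**What the plan says.** Protocol article, Secondary endpoints: the list includes "ICU and hospital length of stay (median". The same list has all-cause mortality as a separate proportion.

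Protocol article, Efficacy: Therapy Intensity Level (TIL) Scale: the daily value takes the worst score per item ("The daily score will be calculated based on the highest score in each item per day (TIL24"), and the patient's value is the "highest TIL24 during the days an ICP monitor is in place (TILmax").

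Protocol article, Statistical analysis: the analysis is by intention to treat with all randomized patients. TILmax is compared by a covariate-adjusted linear model. Secondary outcomes are compared by logistic, ordinal or linear regression. A general sentence adds: "Time-to-event analyses will be undertaken using Kaplan-Meier curves, as well as Cox proportional hazards regression models". It names no endpoint and does not say how death is handled. GOSE at 6 months is tested only if TIL is significant and is not primarily used to declare success.

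Protocol article, Data and safety monitoring: the DSMB sees unblinded mortality.

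The article states no rule for counting a death in length of stay or in TILmax.

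**The concern.** On both measures a lower value is read as better, and on both death ends the observation. A patient who dies on day 2 contributes the same stay as one who goes home on day 2. A median over all randomized patients cannot tell them apart, nor can a linear regression on days. If the time-to-event tools were used for stay with deaths censored, a Kaplan-Meier curve would be read as though the dead could still be discharged.

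For TILmax, cutting short the monitored days can only lower a patient's maximum or leave it unchanged. The Background places "delayed formation of brain edema, mostly seen around the third day after trauma". A patient who dies, or has active treatment withdrawn, before then may never record the score he or she was heading for.

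At stake is the reading of a resource outcome and, more importantly, of the efficacy endpoint that decides whether GOSE is tested. Nothing in the stated success rule links a favourable TIL result to survival.

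**Working it through.** **The plan's own figure.** Inputs from Sample size: difference 2.2, SD 3.2, 90% power, two-sided 5%, about 10% loss. The exact two-sample t-test needs 46 per arm (power 90.4%). 46/0.9 = 51.1, so 52 per arm and 104 in total; 46 × 1.15 = 52.9 gives 53 per arm, the stated 106. The sample size is not in dispute, and 53 per arm is used below.

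**Length of stay.** The article gives no distribution, so all of these inputs are assumptions:

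- survivors' stay lognormal, median 14 days, log-SD 0.7
- usual deaths: the shorter of such a stay and a lognormal time with median 6 days, log-SD 0.7
- extra deaths in one arm fall on days 1 to 3
- usual mortality 30% or 40%, as illustrations only
- comparison by rank-sum test, two-sided 5%, 53 per arm

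Check of the median at 30% usual mortality. At 10.58 days, the survivor fraction discharged is Φ(ln(10.58/14)/0.7) = Φ(−0.400) = 0.345. For usual deaths it is 1 − (1 − 0.345)(1 − Φ(0.810)) = 0.863. Mixture: 0.7 × 0.345 + 0.3 × 0.863 = 0.50. With 10 points of extra early deaths, at 9.09 days: 0.6 × 0.269 + 0.3 × 0.798 + 0.1 × 1 = 0.50.

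| Extra early deaths | Median, 30% usual | Median, 40% usual | Chance of significantly shorter stay |
|---|---|---|---|
| 0 | 10.6 d | 9.5 d | 2% |
| 5 points | 9.9 d | 8.8 d | 8% |
| 10 points | 9.1 d | 8.0 d | 19% |
| 20 points | 7.5 d | 6.5 d | 52% and 58% |

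Ten extra points take about 1.5 days off the median at either usual mortality (10.58 − 9.09 = 1.49; 9.49 − 8.02 = 1.47). The between-arm difference in early deaths drives the result; overall mortality hardly matters.

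**TILmax.** Let q be the share of extra early deaths in one arm and f the fraction of the eventual maximum already recorded at death. Take 8.2, the anticipated mean in Sample size, as the eventual value in these patients (an assumption). Then

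shift = q × 8.2 × (1 − f).

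The standard error at 53 per arm is 3.2 × √(2/53) = 0.62, so the smallest significant difference is 1.96 × 0.62 = 1.22 points. The chance of significance in favour is Φ(shift/0.62 − 1.96). For q = 10%:

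| f | Shift | Chance of significance in favour |
|---|---|---|
| 0 | 0.82 | 26% |
| 0.5 | 0.41 | 10% |
| 0.75 | 0.20 | 5% |
| 1 | 0 | 2.5% |

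To reach 1.22 points, q must be 1.22/8.2 = 15% at f = 0, or 1.22/4.1 = 30% at f = 0.5.

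**Direction.** That formula leaves out escalation of therapy before death. A simulation of daily TIL included it (assumed profile peaking on day 3, 30% usual mortality, extra deaths after one or two monitored days). Mean TILmax was:

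| Escalation on the last day | No extra deaths | 20% extra early deaths |
|---|---|---|
| none | 7.90 | 7.43 |
| 3 points | 8.26 | 8.32 |
| 6 points | 8.95 | 9.60 |

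The arm with more deaths looks better, the same or worse according to what happens before death. The simulated SDs (2.1 to 2.8) are below the 3.2 in the article, so this table shows direction only.

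**The case against.** A reader might infer that, with 30–40% mortality, a treatment that causes early deaths would appear beneficial on both endpoints. The documents do not support that, for three reasons.

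- **TILmax is a maximum.** It is not a sum or an average. If ICP therapy is stepped up before death, the peak is already recorded and the bias disappears or turns against the harmful arm. For TILmax the right word is could.
- **The mortality figure belongs to another population.** The Background says "Patients with s-TBI have a high mortality rate, estimated at 30–40% in observational studies", defined there as GCS 3–8. The trial enrols a "clinical diagnosis of TBI with GCS < 13 on admission", and the article gives no mortality for that group. The bias in any case follows the difference in early deaths between arms.
- **Harm would not be hidden.** Mortality is a secondary endpoint, and the DSMB sees it unblinded at scheduled meetings.

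The entry criteria narrow the TILmax mechanism further: ICP must be monitored and managed for at least 24 hours, and patients brain dead on arrival, or not expected to survive 24 hours and given palliative care, are excluded. They leave deaths between day 1 and the edema peak in the analysis.

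It is also fair to say that the time-to-event sentence is not tied to length of stay, and that a rule for deaths may stand in an analysis plan or full protocol not shown here. That lowers the weight of the point. It does not change what the article itself fixes: a median stay over all randomized patients. Mortality reporting and the DSMB protect patients but do not make that median interpretable.

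**Conclusion.** The point stands as a cheap improvement.

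For length of stay it holds outright in direction: deaths count as short stays, so excess early deaths shorten the median. The size (about 1.5 days and a 19% chance of a significant result for 10 extra points) rests wholly on assumed inputs.

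For TILmax it is conditional. With 10% extra early deaths the spurious gain lies between 0 and 0.82 points, taking 8.2 as the eventual maximum and no escalation before death. That is at most 0.82/2.2 = 37% of the target difference and below the 1.22 points needed for significance. With escalation the sign can reverse. Because the direction is uncertain and this endpoint gates GOSE, one supporting analysis is worthwhile. The primary model and the sample size need no change.

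**What to change.** 1. **Length of stay.** Analyse time to discharge alive from ICU and from hospital with death as a competing event. Alternatively, use days alive and out of ICU or hospital over a fixed period, with deaths scored 0. The raw median can stay as a description.
2. **TILmax.** Keep the planned adjusted linear model as the primary analysis. Pre-specify one supporting rank analysis in which death or withdrawal of active treatment during ICP monitoring takes the worst rank.
3. **Reporting.** Give deaths during ICP monitoring by arm beside the TIL result.

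The supporting analysis informs interpretation; it should not become a further condition for declaring success.

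Cost: some wording and a little extra analysis on data already collected. One drawback is that days alive and out of hospital mixes survival with resource use, which is why the descriptive median is worth keeping.
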